### Perioperative assessment of pain

A numerical rating of perioperative pain experienced by the participants is recorded at baseline, POD 2 and POD 7 using the Numerical Rating Scale-11. Additionally, the Modified Brief Pain Inventory is conducted at 3 months, and the Neuropathic Pain Questionnaire is conducted at 12 months.

### Outcome variables

Primary outcome variable:A between-group comparison of cognitive performance in the early postoperative period (day 7), as measured using the psychomotor-attention composite score of the CogState Brief Battery (CBB)

Secondary outcomes:Between-group comparison of cognitive performance in the early and late postoperative period, as measured using the extended neuropsychological battery, at day 7, 3 months, and 1 year post surgery. Comparisons at each time point will be made to scores obtained at presurgical baselineBetween-group comparison of mood disorder, as measured using the Hospital Anxiety and Depression Scale (HADS), at day 7, 3 months, and 1 year post surgery. Comparisons at each time point will be made to raw scores obtained at presurgical baselineBetween-group comparison of quality of life, as measured using the World Health Organisation Quality of Life – BREF (WHOQOL-BREF) scale, at 3 months, and 1 year post surgery. Comparisons at each time point will be made to raw scores obtained at presurgical baselineBetween-group comparison of delirium, as measured using the Confusion Assessment Method (CAM), on postsurgery days 2 and 7. Incidents of delirium are recorded dichotomouslyBetween-group comparison of postoperative pain, as measured using the Numerical Rating Scale (NRS) on postsurgery days 2 and 7; the Modified Brief Pain Inventory at 3 months, and the Neuropathic Pain Questionnaire at 12 months post surgeryBetween-group comparison of levels of serum neuroinflammation and oxidative stress, including but not restricted to, tumour necrosis factor (TNF)α, IL-1β IL-6, S100β, malondialdehyde, and reduced and oxidised glutathione on postsurgery day 2

### Withdrawal

Participation is entirely voluntary and consent may be withdrawn at any stage. Withdrawal reasons are documented and recorded. Participants are not considered to have withdrawn if they are lost to follow-up, and research staff will attempt to reconnect with participants for subsequent assessments. For example, a participant who is unable to be contacted for the 3-month follow-up is recorded as a missed session, but research staff will attempt to contact the participant for the 12-month follow-up. Participants are withdrawn from treatment and/or assessment if they:Withdraw consent for participationAre unblinded for any purpose prior to the end of the treatment periodAre requested to withdraw by their treating medical team due to interference with their appropriate clinical managementRequire subsequent surgery or anaesthesia prior to measurement of the primary outcome variable

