### Dose and treatment regimen

Administration of NAC in a wide variety of medical settings has been shown to be safe [41, 42]. Whilst there is variation within the literature regarding dose and timing of NAC, recent reviews have suggested NAC administered per os at doses of 2400 mg/day to be efficacious in delivering demonstrable biomarker change with a negligible adverse effect profile [43, 44]. Kuyumcu et al. [33] showed improved oxidative status in abdominal surgery patients with a total dose of 2400 mg of NAC administered intravenously over 2 days prior to surgery. Dose regimens well in excess of 2400 mg/day have been safely explored with some regularity, but are likely to be burdensome during oral administration, a route which offers greater safety [62] and ease of administration than intravenous infusion. Bearing in mind the previously established effective doses, the expected duration of the surgical stress response [42], the oral bioavailability of NAC and the relative ease, safety and cost effectiveness of oral administration, we have chosen a regimen of 1200 mg NAC administered per os twice daily, consisting of two 600-mg capsules in the morning and again in the evening, starting on the day of surgery and continuing for 4 days to a total cumulative dose of 9600 mg. Administration takes place during the patients’ regular morning and evening drug rounds, facilitated by the ward staff and recorded from the patient chart by the research nurses. Placebo is administered in an identical fashion. Medication is dispensed by the pharmacy and administration coordinated by the research nurses, and recorded in the trial records for each participant. Unused medication is returned to the pharmacy for disposal. Episodes of nausea and vomiting are recorded by research staff.

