The literature suggests a strong correlation between the two tasks of the psychomotor-attention composite, detection and identification, for simplicity’s sake assumed to be in the region of *r* = 0.8 is expected (for example, see the similarities present on scores from the research of Hammers et al., 2012; [55] and Lim et al., 2012 [56]). Further, the variances for pre and postsurgery will be standardised to 1. The variance of the composite is calculated as the sum of pre and postsurgical variances plus twice the correlation of the composite tasks; 2 + 2 (0.8) = 3.6. Therefore, to estimate the effect of MCI (and by extension, cognitive change after surgery), we divide the combined effect size for the psychomotor-attention composite by the standard deviation of the effect size, that is the square root of the variance of the composite. From Lim et al., the effect of MCI size of the change in reaction speed for the detection and identification tasks were −0.33 and −0.63, respectively, giving a total reduction in reaction speed effect size of −0.96. Therefore, the total effect of MCI (and by extension, cognitive change after surgery) upon the psychomotor-attention composite is equal to: −0.96/√3.6 = −0.51. Given that NAC is unlikely to improve cognition beyond baseline estimates, it is proposed that NAC may instead ameliorate the severity of cognitive dysfunction compared with placebo. Given the limited available data, we have attempted to estimate an approximate protective effect based on the use of NAC in analogous conditions, such as traumatic brain injury [63]. Additionally, it is unrealistic to assume complete prevention of cognitive dysfunction. Therefore, a relative reduction in severity of cognitive dysfunction of 50 % represents an appropriate compromise to calculate the power. Given the likelihood of significant correlation in pre and postsurgery cognition scores, and in the absence of any identifiable correlation size, it is prudent to include an estimation of correlation patterns in the medium range (*r* = 0.50). A protective effect of NAC of 50 % would then set the expected effect of postoperative cognitive change as modulated by NAC at = −0.255. Assuming an alpha level of 0.05, power of 80 %, and a pre and postsurgical score correlation of 0.5, a sample size of 370 participants will have 80 % power to detect a minimum absolute effect size of 0.255 using an analysis of covariance (ANCOVA) model. This sample size includes approximately equal representation across stratification by age and surgery type for intervention.

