
### Primary analysis

The primary study hypothesis states that the perioperative administration of NAC is superior to placebo in reducing the severity of postoperative dysfunction, as measured by the CBB at POD 7, and compared with baseline. Analysis of the primary outcome will be via ANCOVA, utilising the baseline psychomotor-attention composite score as a covariate. Assumptions of the ANCOVA will be examined through standard tests and residual plots, with transformation of variables being considered if normality of the residuals is not met. The psychomotor-attention composite is made up of the detection and identification tasks on the CBB and represents the reaction time of the participant, where higher scores indicate lower reaction speed and can be used to suggest the presence of impairment. The composite score is calculated by standardising each task score and adding them together. All analyses will be performed as intent-to-treat, in order to best emulate practice settings.

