### Missing or incomplete data

All participants recruited into the study, regardless of treatment group, are to have as much data as possible recorded, as fully as possible in accordance with this protocol. Missing data is monitored so as to avoid bias by attrition or patterns of missing data. All cases of missing data, including instances of nonretention of participants or withdrawal of consent, are to be recorded by research staff. Where data is missing, the frequency and reasons for missing data are to be recorded. Missing data is to be examined to see if there are patterns informative to the study; for example, if certain variables are missed in a systematic way by an identifiable pattern of participant.

In situations where data is missing, for example with participants who are lost to the 12-month follow-up, the data collected up to that point should still be used provided the participant has not withdrawn their consent or requested that the information be removed. If missing data is considered Missing at Random (MAR, i.e. without a pattern), then multiple imputation methods should be used to estimate missing values. The accepted minimum number of imputations is five, to estimate the missing data from existing data. This can be achieved using statistical software. If data appears to be missing in a way that is not random (Missing Not At Random, MNAR), then this data can be examined for potential biases or patterns statistically, and missing values can then be estimated using monotonistic methods.

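### Once dosing has ended, the rule withdrawing participants who need a second operation or anaesthetic can only stop collection of the day-7 outcome, which conflicts with the stated intent-to-treat analysis

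*Protocol article*

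**What the plan says.** The Withdrawal section lists reasons for taking a participant out of treatment, assessment or both, without saying which consequence belongs to which reason. Besides withdrawal of consent, the reasons are being "unblinded for any purpose prior to the end of the treatment" period, a request from the treating medical team on grounds of clinical management, and requiring "subsequent surgery or anaesthesia prior to measurement of the primary outcome variable". The same section says that participants lost to follow-up do not count as withdrawn and will be contacted again; it says nothing similar for withdrawn participants.

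Dose and treatment regimen describes dosing as "starting on the day of surgery and continuing for 4 days". Table 1 schedules the CogState battery, which yields the primary outcome, at postoperative days 7 to 14.

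Primary analysis states: "All analyses will be performed as intent-to-treat, in order to best emulate practice settings". Missing or incomplete data asks for multiple imputation if data are missing at random, which it describes as having no pattern. If they are not, it allows the data to be examined for bias and estimated by methods it calls monotonistic.

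**The concern.** Intent-to-treat needs outcomes from participants as randomised, whatever happens to them afterwards. A rule that stops the primary test because of an event after randomisation works against this at the data-collection stage, where no later analysis plan can recover the score.

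On the protocol's own premises the affected participants are unlikely to resemble the rest. The Inclusion criteria section cites longer surgery as a risk factor for postoperative cognitive dysfunction, and the Background links surgery and anaesthesia to inflammatory signals associated with cognitive impairment. A second operation or anaesthetic adds to that exposure. If such events were more frequent, or more damaging, in one arm, the day-7 contrast among those tested would differ from the contrast among all those randomised. Depending on direction, part of a benefit or part of a harm would go unmeasured.

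**Working it through.** **1. Which consequence can the rule have?** The total dose of 9600 mg at 2400 mg per day gives 9600 / 2400 = 4 dosing days. Counting the day of surgery as the first, these are days 0 to 3. The primary test falls on days 7 to 14. For a second operation or anaesthetic from day 4 until the test, treatment is already complete, so withdrawal can only mean withdrawal from assessment. For an event during dosing, and for unblinding (limited to the treatment period), withdrawal from treatment alone remains a possible reading. For a treating-team request the text does not settle it.

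**2. The plan's own sample size.** The inputs from Sample size determination are alpha 0.05, 80% power, a correlation of 0.5 between baseline and follow-up scores, and unit variances ("the variances for pre and postsurgery will be standardised to 1"). The claim drawn from them there is that "a sample size of 370 participants will have 80 % power to detect a minimum absolute effect size of 0.255". A two-sided test is assumed, since sidedness is not stated.

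- Residual SD after baseline adjustment: √(1 − 0.5²) = 0.866.
- n per arm = 2 × (1.960 + 0.842)² × 0.75 / 0.255² ≈ 181.1, rounded up to 182, so 364 in total. The stated 370 is reproduced to within 2%.
- Power at 185 per arm: Φ(0.255 / (0.866 × √(2/185)) − 1.960) = Φ(0.872) = 80.8%.

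**3. Loss of power if the same fraction is untested in both arms** (fractions assumed):

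| Untested | Participants tested | Power |
|---|---|---|
| 0% | 370 | 80.8% |
| 2% | 363 | 80.1% |
| 5% | 352 | 78.8% |
| 10% | 333 | 76.6% |

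The section states no allowance for withdrawals.

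**4. Shift in the contrast.** Higher composite scores mean slower responses, so let D be the placebo mean minus the NAC mean (positive favours NAC). Let w be the fraction untested in an arm and k how much worse, in SD, those participants would have scored than the tested participants of the same arm. Each arm's full mean is its tested mean plus k × w, hence

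D(all randomised) = D(tested) + k(placebo) × w(placebo) − k(NAC) × w(NAC).

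With a common k, the size of the shift is k × |w(placebo) − w(NAC)|. The documents give neither w nor k; all values below are assumptions. The value 0.51 is the effect of mild cognitive impairment used in the sample size section.

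| w placebo | w NAC | k | Shift (SD) | Share of 0.255 |
|---|---|---|---|---|
| 5% | 5% | any common value | 0 | 0% |
| 5% | 3% | 0.5 | 0.010 | 4% |
| 7% | 3% | 0.51 | 0.020 | 8% |
| 5% | 2% | 1.0 | 0.030 | 12% |
| 10% | 5% | 1.0 | 0.050 | 20% |

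With the higher rate on placebo, as here, the tested-only contrast understates a benefit of NAC. With the rates reversed it overstates it by the same amount.

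**5. Does imputation restore the contrast?** If participants re-operated on after dosing have no day-7 score, imputation under missing at random takes their values from participants of the same arm without the event. That sets k to zero and reproduces D(tested), not D(all randomised). By the plan's own description, missingness caused by re-operation has a pattern and so belongs in the not-at-random branch. That branch names no model for how the unobserved scores differ: monotone describes a pattern of missingness, not its cause.

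**The case against.** The strongest reply is that the wording permits withdrawal from treatment alone, that nothing in the article removes withdrawn participants from the analysis set, and that the missing-data section keeps what was already collected and provides for both kinds of missingness. Much of this stands:

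- A reader might infer that every trigger ends assessment. The text does not support that for unblinding or treating-team requests. The argument from dates applies only to a second operation or anaesthetic after dosing.
- A reader might infer that these participants are excluded from the comparison. What the rule does is narrower: their day-7 score is not collected, and an imputed value may stand in for it.
- A reader might set the rule against the statement "All participants recruited into the study, regardless of treatment group, are to have as much data as possible recorded". That sentence goes on to make the recording subject to the protocol, and hence to the withdrawal rules, so it is not a clear contradiction.
- A reader might infer that the 3- and 12-month visits are lost too. The article does not say how long withdrawal from assessment lasts.
- A reader might infer that NAC changes the rate of re-operation or unblinding. No section says so. The only treatment-related route to withdrawal that the article names is nausea and vomiting, in the Discussion.
- The larger shifts rest on a k of 1 SD, about twice the 0.51 taken for mild cognitive impairment.

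What does not stand is the reply for re-operation after dosing. There the treatment-only reading is unavailable, and neither imputation branch clearly recovers the missing scores. Nor is this a detail to be left to an analysis plan, because it decides whether the test is done.

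**Conclusion.** The conflict is real but limited. For a second operation or anaesthetic after the 4 dosing days and before the primary test, the Withdrawal section stops outcome collection for a post-randomisation reason, against the intent-to-treat principle under Primary analysis. For unblinding and treating-team requests the fault is ambiguity.

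The size cannot be derived from the documents. Under the assumed rates and declines it runs from about 0.01 to 0.05 SD, or 4% to 20% of the 0.255 SD target. It is zero if both the rates and the extra decline are equal in the two arms; the cost is then a modest loss of power. A stronger claim, that the primary result will be materially biased, would need a difference between arms that the article neither states nor implies. The wording should be fixed because the remedy is cheap and an untested participant cannot be recovered later, but the evidence does not make it an essential correction.

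**What to change.** In the Withdrawal section, separate stopping of trial treatment from stopping of assessment, and leave the treatment-stopping criteria unchanged. State that a second operation or anaesthetic, or unblinding, does not by itself end assessment. These participants should be tested at the scheduled visits unless they withdraw consent for follow-up, and analysed in their randomised arm. Record each event with its date. Report an analysis that excludes participants with a second anaesthetic before the primary test only as a sensitivity analysis.

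The treating-team criterion must be reconciled with the intent-to-treat statement by saying what it means for assessment, without altering the clinical rule.

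The cost is a short amendment, a few more assessments at visits already in the schedule, and slightly more variance in the primary outcome from participants with a complicated course.

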### Adverse events

Adverse events (AEs), serious adverse events (SAEs), and suspected unexpected serious adverse reaction (SUSAR) monitoring and reporting are conducted in strict accordance with the processes established by both governing ethics committees.

AEs are recorded from the time that informed consent has been obtained until the end of the 12-month study period. For each, the following parameters are described:The investigator’s assessment of the causal relationship between the event and the investigational treatmentA description of the AE, including its nature, start and stop date, action taken with regards to the investigational treatment, intensity and outcomeA statement if the AE fulfils the criteria for an SAE or a SUSAR

Intensity is determined according to the following categories:Mild: an AE which is easily tolerated by the participant, causing minimal discomfort and not interfering with everyday activitiesModerate: an AE which is sufficiently discomforting to interfere with everyday activitiesSevere: an AE which is incapacitating and prevents everyday activities and/or requires therapeutic intervention, i.e. use of a prescription drug or hospitalisation

### Follow-up of adverse events and SUSARs

AEs are followed up until either they are resolved, or persist despite cessation of the trial medication and its elimination from the body (given that the half-life of NAC is roughly 6 h, this is estimated to take 2 days). AEs may be followed up for longer at the discretion of the investigators. 

### Reporting of serious adverse events and SUSARs

Reporting of SAEs to regulatory authorities is done within the requisite 24-hour period by an investigator in accordance with local regulations. A copy of the SAE report is sent to the Barwon Health Human Research and Ethics Committee, the sponsor and the principal investigator. If unblinding is required, a report will also be sent to the Therapeutic Goods Administration.

### Mortality reporting

Regardless of causality or which randomisation arm the participant is assigned to, all cases of mortality are reported to the Data Safety Management Board and regulatory authorities.

### Termination and safety

It is intended that the trial will run for the projected duration of 4 years from recruitment of the first patient. A DSMB has been established for this study and is independent of the investigators. Investigators provide intermittent reports to the DSMB with any information relating to safety analyses, and monitor instances of adverse. The DSMB provides recommendations regarding the continuation of the study.

### Sample size determination

Due to variations in definitions and cut-off criteria, measuring the effects of POCD, in the context of previous literature, is extremely difficult. Additionally, there is no literature available examining the use of the CBB for the detection of POCD, despite being theoretically suited to the task. However, literature that examines differences between healthy controls and mild cognitive impairment (MCI) provides a close approximation of the quantifiable effects of cognitive change after surgery. An examination of the available research utilising the CBB provides an estimated effect size of cognitive change in comparison to healthy controls, MCI, and Alzheimer’s disease participants.

The literature suggests a strong correlation between the two tasks of the psychomotor-attention composite, detection and identification, for simplicity’s sake assumed to be in the region of *r* = 0.8 is expected (for example, see the similarities present on scores from the research of Hammers et al., 2012; [55] and Lim et al., 2012 [56]). Further, the variances for pre and postsurgery will be standardised to 1. The variance of the composite is calculated as the sum of pre and postsurgical variances plus twice the correlation of the composite tasks; 2 + 2 (0.8) = 3.6. Therefore, to estimate the effect of MCI (and by extension, cognitive change after surgery), we divide the combined effect size for the psychomotor-attention composite by the standard deviation of the effect size, that is the square root of the variance of the composite. From Lim et al., the effect of MCI size of the change in reaction speed for the detection and identification tasks were −0.33 and −0.63, respectively, giving a total reduction in reaction speed effect size of −0.96. Therefore, the total effect of MCI (and by extension, cognitive change after surgery) upon the psychomotor-attention composite is equal to: −0.96/√3.6 = −0.51. Given that NAC is unlikely to improve cognition beyond baseline estimates, it is proposed that NAC may instead ameliorate the severity of cognitive dysfunction compared with placebo. Given the limited available data, we have attempted to estimate an approximate protective effect based on the use of NAC in analogous conditions, such as traumatic brain injury [63]. Additionally, it is unrealistic to assume complete prevention of cognitive dysfunction. Therefore, a relative reduction in severity of cognitive dysfunction of 50 % represents an appropriate compromise to calculate the power. Given the likelihood of significant correlation in pre and postsurgery cognition scores, and in the absence of any identifiable correlation size, it is prudent to include an estimation of correlation patterns in the medium range (*r* = 0.50). A protective effect of NAC of 50 % would then set the expected effect of postoperative cognitive change as modulated by NAC at = −0.255. Assuming an alpha level of 0.05, power of 80 %, and a pre and postsurgical score correlation of 0.5, a sample size of 370 participants will have 80 % power to detect a minimum absolute effect size of 0.255 using an analysis of covariance (ANCOVA) model. This sample size includes approximately equal representation across stratification by age and surgery type for intervention.

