## Methods and design

A single-centre, randomised, double-blind, placebo-controlled clinical trial. A total of 370 participants are randomised into either a placebo or treatment (NAC) group in a 1:1 ratio.

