### Randomisation, allocation, and concealment

Once consent is confirmed, participants are randomised to a treatment group. Randomisation is stratified by surgery type (orthopaedic or nonorthopaedic) and age (less than 80 years or 80 years or older) to provide four strata for the study. The allocation code was produced by an independent researcher prior to the commencement of recruitment and was generated by a computer-generated list, using permuted block randomisation with variable block sizes. The allocation code is concealed to all trial personnel, with the exception of the dispensing pharmacist. The pharmacist allocates the participant number, based on the relevant stratum and holds the code if unblinding is required, but is not involved in data collection. All other relevant persons, including investigators, research assistants, research nurses, and participants are blind to the treatment allocation until the end of the data analysis.

To aid treatment concealment, all trial materials appear identical. Further, the placebos have been dusted with a nontherapeutic amount of NAC to assist with matching odours (given that NAC has a strong odour). The placebos and NAC capsules are identical in size, taste, and appearance. All trial medication is provided in identical bottles. Any unused medication is returned to the pharmacy for auditing.

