## Discussion

Our study is the first randomised controlled clinical trial on the efficacy of perioperative NAC administration upon cognition. Because the trial will aim to recruit 370 participants and primarily examine the efficacy and safety of NAC, we consider this to be a phase 2 trial.

Australia’s population is ageing, and will continue to require greater numbers of surgical procedures. The commonness of cognitive dysfunction after surgery [1, 3, 4, 38], and the significantly increased risk of expedited morbidity and mortality [5–8], provide a strong community motivation to investigate potential interventions and it is hoped that NAC may fulfil that need.

The PANACEA trial is not without limitations, particularly the risk of attrition common in longitudinal studies. The potential for increased risks of nausea and vomiting may also result in participant withdrawal. Whilst all reasonable attempts to reduce the influence of attrition bias are employed, the possibility cannot be ruled out.

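### The 370 in the power statement is in effect the number to be analysed, but it is also the number randomised, with no allowance for missing day-7 scores

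*Protocol article*

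**What the plan says.** The protocol article, Sample size determination, states that "a sample size of 370 participants will have 80 % power to detect a minimum absolute effect size of 0.255" under an ANCOVA. The inputs are in the same section: "Assuming an alpha level of 0.05", 80% power, "a pre and postsurgical score correlation of 0.5", and variances set so that "the variances for pre and postsurgery will be standardised to 1". A 50% protective effect "would then set the expected effect of postoperative cognitive change as modulated by NAC at = −0.255". The only remark after the calculation concerns representation across the strata; nothing is said about dropout or missing outcomes.

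Methods and design uses the same figure for randomisation: "A total of 370 participants are randomised into either a placebo or treatment (NAC) group in a 1:1 ratio". The abstract gives 370 as the recruitment target.

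The Discussion names as a limitation "particularly the risk of attrition common in longitudinal studies" and adds that nausea and vomiting may lead to withdrawal. The Withdrawal section lists reasons for withdrawal from treatment, assessment or both. One of them, a further operation or anaesthetic before the primary outcome is measured, can by definition only act before that measurement. Missing or incomplete data plans multiple imputation for data judged missing at random. No section gives a rate of loss.

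**The concern.** A power statement refers to the patients who contribute to the analysis. If 370 is what the formula returns with no inflation, and 370 is also the number randomised, the stated 80% holds only if practically every randomised patient has a usable baseline and day-7 score on the psychomotor-attention composite. The patients are aged 60 or older, and the test is a computerised reaction-time task about a week after major surgery.

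At stake is how the result is read. A trial that reports 80% power for 0.255 but had nearer 75% invites a null result to be taken as stronger evidence against that effect than it is.

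**Working it through.** **Inputs**, all from Sample size determination unless noted:

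- Alpha 0.05. Sidedness is not stated. I take it as two-sided, because a one-sided ANCOVA would need only 286 in total and does not reproduce 370.
- Power 80%; 1:1 allocation (Methods and design).
- Effect d = 0.255, from 0.51 × 0.50. Unrounded: 0.96/√3.6 = 0.506, and half of that is 0.253.
- SD 1 and correlation r = 0.5, so the ANCOVA residual variance is 1 − 0.5² = 0.75 and the residual SD is 0.866.

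I take the effect size and the correlation as given; this check does not test how they were derived.

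**Step 1: reproduce the plan's figure.** By the normal approximation, n per arm = 2(z₀.₉₇₅ + z₀.₈₀)²(1 − r²)/d².

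- d = 0.255: 2(1.960 + 0.842)² × 0.75/0.255² = 181.1, so 182 per arm and 364 in total.
- d = 0.253: 184.0 per arm before rounding, so 368 in total.

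By the noncentral t with N − 3 degrees of freedom and noncentrality d/(0.866 × √(4/N)):

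| N analysed | Power at 0.255 | Power at 0.253 |
|---|---|---|
| 364 | 79.99% | 79.4% |
| 366 | 80.2% | 79.6% |
| 370 | 80.6% | 80.0% |

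The protocol's 370 is therefore reproduced. It is the uninflated number for the unrounded effect, and 4 to 6 patients above the need at the stated 0.255. An analysis without the baseline covariate, or of change scores at r = 0.5, would need 484, so no other two-sided reading hides an allowance inside 370.

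**Step 2: the margin.** 370 − 366 = 4 and 370 − 364 = 6, that is 1.1% to 1.6% of 370. At 0.253 there is none.

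**Step 3: loss of day-7 scores.** The documents give no rate, so these losses are assumptions. N analysed = 370 × (1 − loss); power and detectable effect are by noncentral t.

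| Assumed loss | N analysed | Power at 0.255 | Effect detectable with 80% power |
|---|---|---|---|
| 0% | 370 | 80.6% | 0.253 |
| 2% | 362.6 | 79.8% | 0.256 |
| 5% | 351.5 | 78.6% | 0.260 |
| 10% | 333 | 76.4% | 0.267 |
| 15% | 314.5 | 74.0% | 0.274 |
| 20% | 296 | 71.4% | 0.283 |

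**Step 4: for comparison, what keeping 80% would take.** 370/(1 − loss) gives 390, 412, 436 and 463 randomised at 5, 10, 15 and 20% loss.

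**The case against.** **There is no arithmetic error.** This stands. The power sentence is conditional on its inputs, and with 370 analysed they give 80.6%. A reader might infer that the stated power is miscalculated; the check shows that it is not. Nor is 370 exactly the number needed at the stated effect: that holds only for 0.253, a figure the protocol does not print.

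**Attrition is named as a risk, not forecast.** This also stands. The Discussion speaks of longitudinal attrition in general, gives no rate and does not tie it to day 7. The example under Missing or incomplete data is loss to the 12-month visit. The powered endpoint has a window of postoperative days 7 to 14 (Table 1), and home visits are possible, so early loss may be well below 12-month loss. At 5% the cost is about 2 points.

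**Withdrawal need not remove the outcome.** Partly right. The rules allow withdrawal from treatment alone, and the primary analysis is by intention to treat, so a patient who stops capsules may still be tested. But the rule on further surgery or anaesthesia is tied to the period before the primary measurement, and nausea would arise during the 4 days of dosing.

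**Multiple imputation helps.** It can recover some information, for instance through the 3-month composite, but not all of it. It does not give back the power of a complete sample.

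**Other inputs matter as much.** True. With all 370 analysed, a correlation of 0.4 gives 76% power and 0.6 gives 86%; 0.56 with 10% loss returns to about 80%. That makes the 80% approximate in both directions, whereas missing outcomes can only lower it.

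**A stronger reading concerns the timing of randomisation.** The protocol says "Once consent is confirmed, participants are randomised to a treatment group", and recruitment is in presurgical clinics. A reader might infer that cancelled operations and missed baseline tests become losses after randomisation, and that randomisation should be moved. The documents shown do not support this: they give no interval from consent to randomisation or surgery, do not fix the order of baseline testing and randomisation, and the flow chart is not visible.

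**Conclusion.** The point holds as a missing allowance, not as a calculation error. One figure, 370, serves both as the number that must be analysed and as the number randomised, in a protocol that foresees withdrawals, some of which can fall before the primary measurement. Power for 0.255 drops below 80% once more than about 1 to 2% of randomised patients lack a day-7 score. The shortfall is slight at 5%, about 4 points against 80.6% at 10%, and about 9 points at 20%.

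This rests on a two-sided test, the protocol's own effect size and correlation, losses spread evenly over the arms, and little information regained by imputation. The loss rates are an assumed range. The 3- and 12-month comparisons are secondary and lie outside the power statement, so later attrition does not bear on this figure.

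**What to change.** Keep 370 and restate the power in Sample size determination, separating the number randomised from the number analysed. For example: 370 randomised; if 10% (assumed range 5 to 20%) lack a day-7 score, 333 are analysed, giving about 76% power for 0.255, or 80% power for 0.267. State that the test is two-sided if that is what was intended, and replace the assumed 10% with the trial's own pooled, blinded day-7 completion rate if it is available.

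The cost is a less favourable headline figure and a short text change. No extra patients are needed, and no change to the time of randomisation is proposed. Enlarging the trial to hold 80% would take about 390 to 463 randomised over the same range; that is an option, not a requirement of this point.
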